## Treatment and follow-up of adverse event

Adverse event should be actively treated, regardless of the causal relationship between the event and investigational product. Acceptable clinical therapeutic measures should be taken for treatment of the patient experiencing adverse event. If it is absolutely necessary to use the medical measures rejected in the study project, it should be discussed with the sponsor if the patient needs to be withdrawn from the study.

Adverse event will be followed up not only in treatment period, for some subjects, the adverse event related with the investigational product that is still present after end of the study should be followed up on an ongoing basis until any one of the following conditions is met:

1. The event is resolved;
2. The event is stable;
3. The event returns to baseline level;
4. The event can be attributed to a drug other than the investigational product or unrelated with the study behavior;
5. More information is unlikely to be obtained (the patient refuses to provide more information, or as proven by the evidence, the patient is still lost of follow-up in despite of utmost effort).

## Serious Adverse Event

### Serious adverse event definition

Serious adverse event (SAE) is defined as the following important medical event occurred at any dose:

1. Requiring hospitalization or prolongation of existing hospitalization;
2. Disability;
3. Affecting working capacity;
4. Being life-threatening or death;
5. Leading to congenital deformity;
6. An important medical event (for example, it may affect the subject or require medication/surgery to prevent the above outcomes).

Some events requiring hospitalization or prolongation of existing hospitalization may not be serious adverse events, including hospitalization for other reasons rather than adverse event, hospitalization for scheduled surgery prior to the study or the purpose of other treatment or examination.

When determining whether an event is an important medical event, scientific medical judgment needs to be made. An important medical event may not be immediately life-threatening and/or may not lead to death or hospitalization. However, if this event is determined to possibly endanger the subject or requires interventional measures to prevent one of the above outcomes of one adverse event, this important medical event should be reported as serious adverse event.

### Management and record of serious adverse event

In case of any serious adverse event occurred during the study, regardless of its relationship with the study and investigational product, investigators should make a full evaluation of the event immediately, complete serious adverse event report form and fax to Shandong Luye Pharma Co., Ltd. within 24 hours, whilst reporting to the ethics committee, CFDA, Shandong Food and Drug Administration and the provincial Food and Drug Administration where the study unit is located within 24 hours.

## Pregnancy

The clinical study pregnancy form must be used to report any pregnancy occurred during participation in the study. In order to ensure subject’s safety, each pregnancy must be reported to Shandong Luye Pharma Co., Ltd. within two weeks after awareness of it. The pregnancy must be followed up, as to determine the prognosis and state of the mother and infant (including early termination of pregnancy). Complications of pregnancy and targeted termination of pregnancy for medical reasons must be reported as AE or SAE. Spontaneous abortion must be reported as SAE.

If the subject has any pregnancy related SAE after completion of the study, which is learnt by the investigator and judged by the investigator as possibly related with the investigational product, it must be reported to Shandong Luye Pharma Co., Ltd. immediately.

In addition, if any female partner of male subject is pregnant during participation of the male subject in this study, the investigator must try to collect the data on the pregnancy. As described above, data on pregnancy must be reported to Shandong Luye Pharma Co., Ltd.

# Unblinding

MagMin central randomization system has the function of unblinding at the same time. Prior to the start of the study, the principal investigator at each site will be allocated one emergency ublinding code by system administrator, as to be used in case of emergency blinding (one more code can be distributed successively after use). After end of the study, the unblinding and randomization will be submitted simultaneously for archival. It is specified for unblinding individual cases in case of emergency that the responsible investigator at sub-site will report to the monitor, sponsor and principal investigator to determine emergency unblinding, when serious adverse event or death occurs, or urgent rescue is needed.

It is specified for the preservation of blind base that Level I is the group corresponding to drug numbers and Level II is the treatment corresponding to the two groups. Two levels of blind base will be sealed separately, in triplicate, and kept by the leading unit and the sponsor, respectively, and for submission.

It is specified for unblinding that after all the study data have been verified and locked, the statistical plan will be discussed by the principal investigator, statisticians and the sponsor jointly, and the first unblinding will be carried out, the three parties will sign on the blind base.

Upon unblinding, any modification to the database needs to be approved by the principal investigator, statisticians, data administrator and the sponsor in a written form.

# Data managementand statistical analysis

## Data management

### Data collection and transfer

Investigators must ensure the data are true, complete and accurate.

Except the data collected directly by computer or automatic instrument, all the data generated from actual study need to be recorded in the form, arranged and bound at any time. All the data records are dated and signed by the recorder.

Investigators will fill in the CRF and sign in a timely, complete and accurate manner in accordance with the subject’s orginal condition, the CRF must be completed for all the included cases. All the items on CRF need to be filled in and must not be blank or missed; investigators can only underline, note new data on the side, provide the reason, sign and date when doing any change, and can not wipe or cover the original record. Laboratory examination items are complete.

### Data Monitoring

Monitors wil monitor the whole course of the study as required in the protocol. Monitors will review the original data and CRF, as to ensure the clinical study data are recorded in a timely, accurate, standardized and complete manner, ask investigators to correct in time if there is any error or omission. The original record should be clearly visible with investigator’s signature and date during the modification.

### Data transfer

The CRF verified by monitors should be signed by monitors, and submitted to data administrator in time. The transfer of completed CRF across investigators, monitors and data administrator should be documented, and signed and dated by the handover person.

### Data entry and modification

Data entry and management will be the responsibility of data administrator at the statistical unit. After receipt of the first copy of CRF, data administrator shall establish one dedicated database for data entry and management. The database naming should be standardized, easy to read and easy to search. Data need to be entered and proofread independently in duplicate.

### Data Lock

The data will be locked upon confirmation by the principle investigator, the sponsor, statistical analysis personnel and monitors. The data file locked shall no more be changed. The questions found after lock of database can be modified in the statistical analysis program upon confirmation.

### Data archival

After completion of data entry and verification as required, CRF should be filed for preservation in the order of numbering, electronic data files, including database, inspection procedure, analysis procedure, analysis result and coding bood, shall be backed up on different recording media for proper storage.

## Statistical analyses

After study protocol is finalized, the statistical analysis plan will be generated by professional statisticians through the discussion with principal investigator.

### Analysis set of clinical trial

The analysis set defined for this study is as below:

1. Full analysis set (FAS)

It includes all the randomized subjects who were administrated at least 1 dose of double-blind study drug and had primary efficacy evaluation at baseline and at least one primary efficacy evaluation after the first dose of double-blind treatment. Unless otherwise specified, LOCF (last observation carried forward) will be used for the missing value imputation in the FAS.

FAS is the primary analysis data set for this trial.

1. Per protocol set (PPS)

It includes all the subjects who completed visit 6 and have no major protocol deviation.

1. Safety set (SS)

It includes all the subjects who were randomized and administrated at least one dose of the double-blind study drug. Subjects who were dispensed study drug but did not administrate any study drug will not included in SS.

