## Sample size calculation

This is one phase 2 dose-exploratory study, according to the requirements of CFDA drug regulatory regulationsat, at least 200 valid cases need to be completed, and considering a (20-30)% fall-off rate, a total of 260 cases are expected to be enrolled in consideration of the possible drop-out rate of 30% during the study, and 1:1:1:1:1 randomized to Ansofaxine Hydrochloride Extended Release Tablet 40, 80, 120 and 160 mg dose groups or placebo group, there will be at least 52 screening eligible cases in each group.

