# Follow-up procedure

The follow-up schedule and content are seen in Figure 1 in this study, the patients may be followed up for safety at any time during that period.

Fig. 1 Study flow chart

|  | **Screening/wash-out period^1^** | **Baseline** | **Double-blind treatment period (6 weeks)** | | | |
| --- | --- | --- | --- | --- | --- | --- |
| **Visit** | **Visit 1**  **-14 ~ -1 d** | **Visit 2**  **0d** | **Visit 3**  **7 ± 1d** | **Visit 4**  **14 ± 1d** | **Visit 5**  **28 ± 3d** | **Visit 6/ at termination**^2^  **42 ± 3d** |
| Informed consent | × |  |  |  |  |  |
| Inclusion and exclusion criteria | × | × |  |  |  |  |
| General information | × |  |  |  |  |  |
| Medical history and psychiatric symptoms | × |  |  |  |  |  |
| DSM-IV-TR diagnostic criteria | × |  |  |  |  |  |
| Randomization |  | × |  |  |  |  |
| HAM-D_17_ | × | × | × | × | × | × |
| HAMA |  | × | × | × | × | × |
| CGI-S | × | × | × | × | × | × |
| CGI-I |  |  | × | × | × | × |
| VAS-PI |  | × | × | × | × | × |
| Physical examination | × |  |  |  |  | × |
| Vital signs^3^, body weight | × | × | × | × | × | × |
| Laboratory test^4^ | × |  |  | × |  | × |
| FT3, FT4,TSH | × |  |  |  |  |  |
| HbsAg, anti-HCV | × |  |  |  |  |  |
| Urine pregnancy test^5^ | × | × |  |  |  | × |
| Urine drug screening^6^ | × |  |  |  |  |  |
| ECG | × | × |  | × |  | × |
| AE record(s) | × | × | × | × | × | × |
| Recording of concomitant medication | × | × | × | × | × | × |
| Record of drug dispensation and administration | ×^7^ | × | × | × | × | × |
| Record of end of study |  |  |  |  |  | × |

Note:

1. Screening/wash-out period: on Day -14~-1, all the subjects will be dispensed with the drugs for wash-out period on Day -8 and enter the 7-day wash-out period (-7 ± 1d).
2. For the subjects who terminate the study prematurely, they will complete the last visit in accordance with the evaluation content at the end of Week 6 (Day 42).
3. Respiratory frequency, axillary temperature, pulse rate and blood pressure in supine and orthostatic position need to be measured (please see 8.2.1 for relevant description).

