### Analysis of Efficacy

The final treatment evaluation will be the primary evaluation for all the primary and secondary efficacy variables. The double-blind treatment starts from the first dose of study drug, until the last dose of study drug. PPS and FAS are used for the analysis of efficacy. The analysis of PPS is based on the observed data. Unless otherwise specified, LOCF (last observation carried forward) and the observed data will be used for analysis of FAS.

The missing items of observations on the efficacy scale will be processed as described below: if up to 20% of the items are missing on one scale, the total score can be derived by multiplying the average of the available items by the total number of items. If more than 20% of the items are missing, the total score on this scale will be considered as missing. The missing total scores will be imputed using the LOCF method. For observed case (OC) analysis, the missing total scores will not be imputed. The baseline score will not be used to carry forward.

In the statistical model using study site as one independent variable the site with small number of subjects may be pooled. The anlaysis will be performed after the sites were pooled. The rules of pooled site will be provided in the statistical analysis plan, if necessary. In addition, this study is one exploratory analysis, and no adjustment of multiple tests will be carried out.

1. Analysis of the primary endpoints

The primary endpoint is the change in the total score of HAM-D_17_ scale from baseline at the final treatment evaluation, and the statistics including the number of subjects, mean, standard deviation, median, minimum and maximum will be calculated.

This is one dose-effect exploratory study, α for type I error is set as 0.1.

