In the exploratory analysis of efficacy in each dose group, the mean plots for the efficacy endpointover time will be created firstly (visit time as the x axis, the mean HAM-D_17_ scale in each group as the y axis), as to observe the trend of change in the therapeutic effect over time in each dose group, and repeated measure analysis of variance (time as intragroup factor, treatment group as intergroup factor) will be used to explore the statistical significance among the doses; secondly, the mean plots for the efficacy endpoint among dose will be created (dose as the x axis, the mean HAM-D_17_ scale at the end of Week 6 as the y axis), and ANCOVA model is used to compare the change in the total score of HAM-D_17_ scale from baseline at the end of Week 6 between treatment groups, using total score of HAM-D_17_ at baseline as covariate, treatment group and site as fixed effect, as to explore of the relationship between efficacy and dose (linear growth, exponential growth or "S" growth).

1. Analysis of the secondary endpoints

The scores on each scale will be summarized using the number of subjects, mean, standard deviation, median, minimum, maximum and interquartile range by visit; the number of subjects and percentage will be used for the response rate and remission rate by visit. The analysis method for each secondary endpoint variable is as below:

CGI-I and CGI-S scale: ANOVA will be used for CGI-I, the model will be include treatment group and site as factors; ANCOVA will be used for CGI-S, the model considers the change from baseline as dependent variable, treatment group and site as fixed fators, and baseline of CGI-S as covariate variable.

HAMA and VAS-PI: ANCOVA model will be used to evaluate the change from baseline in the total score of HAMA scales, psychological anxiety score on HAMA scale, somatic anxiety score on HAMA scale and change in each subcomponent of VAS-PI at each time point, the model factors are treatment group and site, the corresponding baseline score is the covariate.

HAM-D_17_ response rate: HAM-D_17_ responder is defined as the subject with HAM-D_17_ score reduced by ≥50% from baseline. Cochran-Maenszel-Haensel test (corrected by site) will be used to analyze the response rate at each time point.

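### LOCF is the default for the primary Week 6 dose comparison with 20-30% drop-out planned for; if drop-out differs by dose it can bias the dose contrasts and ranking

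*Protocol*

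**What the plan says.** Under Analysis set of clinical trial (section 11.2) the protocol says that "FAS is the primary analysis data set for this trial" and that, unless specified otherwise, "LOCF (last observation carried forward) will be used for the missing value imputation in the FAS". Analysis of Efficacy repeats the rule for the scales: "The missing total scores will be imputed using the LOCF method". It adds that "The baseline score will not be used to carry forward", and the FAS requires at least one post-baseline primary assessment. The same section says that "LOCF (last observation carried forward) and the observed data will be used for analysis of FAS", without saying which of the two decides.

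Sample size calculation (4.6) allows for a "possible drop-out rate of 30% during the study" and gives a range of 20-30% in the same sentence. Objectives (section 2) makes finding the optimal dose the primary objective. Dose adjustment (6.5) does not allow the dose to be changed.

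On the time point, Analysis of Efficacy first makes the final treatment evaluation primary. Its dose-response paragraph, like the Statistical analyses row of the Abstract, then applies ANCOVA to the change at the end of Week 6. No likelihood-based mixed model or multiple imputation is named.

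**The concern.** HAM-D17 is measured at Weeks 1, 2, 4 and 6. If scores fall steadily, LOCF enters an early leaver in the Week 6 comparison with a score from before most of the improvement. A dose with more, or earlier, drop-out then looks less effective than it is, and the imputed values are analysed as if observed.

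The ranking of four active doses is what this trial is meant to deliver, so a bias that depends on each arm's drop-out pattern bears on its main decision. The protocol makes dose-related drop-out plausible, though it does not establish it: steady-state exposure is dose proportional, nausea, vomiting and diarrhoea judged possibly related to the drug were seen in phase I, and doses are fixed.

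**Working it through.** **1. How many subjects could be affected.** Inputs from section 4.6: 200 valid cases, 30% drop-out, 260 enrolled, 52 per arm. The total is reproduced as 200 × 1.30 = 260. At 30% drop-out, 260 × 0.30 = 78 subjects (15.6 per arm) could lack a Week 6 score; at 20%, 260 × 0.20 = 52 (10.4 per arm). These are upper bounds for imputation, because subjects with no post-baseline score leave the FAS.

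**2. Expected LOCF bias.** The protocol gives no trajectory, so these are assumptions: 30%, 55%, 85% and 100% of the Week 6 change is reached at Weeks 1, 2, 4 and 6. With drop-out proportion d and Week 6 change Δ:

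LOCF mean = (1 − d) × Δ + d × (weighted mean of the Week 1, 2 and 4 changes)

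- Last visit at Week 1/2/4 in 50/30/20% of leavers (early): 0.5 × 0.30 + 0.3 × 0.55 + 0.2 × 0.85 = 0.485, so LOCF mean = Δ × (1 − 0.515d).
- Leavers spread evenly: (0.30 + 0.55 + 0.85)/3 = 0.567, so LOCF mean = Δ × (1 − 0.433d).

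For two doses with the same true change of −13, the false difference is 13 × 0.515 (or 0.433) × the difference in drop-out:

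| Difference in drop-out | Early leavers | Even spread |
|---|---|---|
| 5 points | 0.33 | 0.28 |
| 10 points | 0.67 | 0.56 |
| 20 points | 1.34 | 1.13 |

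**3. A second trajectory.** Assumed means are 25 at baseline and 21, 18, 15 and 12.5 at Weeks 1, 2, 4 and 6. Leavers after those first three visits are frozen 8.5, 5.5 and 2.5 points above their arm's Week 6 mean. Drop-out among those remaining is 14/10/8% in one arm and 5/6/7% in the other.

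- First arm: 0.140 × 8.5 + 0.086 × 5.5 + 0.062 × 2.5 = 1.82; completers 0.86 × 0.90 × 0.92 = 71%.
- Second arm: 0.050 × 8.5 + 0.057 × 5.5 + 0.063 × 2.5 = 0.90; completers 0.95 × 0.94 × 0.93 = 83%.

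The false deficit is 1.82 − 0.90 = 0.92 points for a drop-out difference of about 12 percentage points. In 400 simulated trials (52 per arm, SD 3.5-7.2, correlation 0.75^lag) the mean LOCF difference was 0.92 (SD 1.36). A likelihood-based multivariate-normal estimate gave −0.01 (SD 1.41).

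**4. Effect on the ranking.** Assumed true changes: placebo −10, 40 mg −11, 80 mg −12, 120 mg −13, 160 mg −13.5; trajectory shape as in step 2.

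- Equal 30% drop-out, early leavers: the order is kept, and the 160 mg contrast with placebo shrinks from −3.5 to −3.5 × (1 − 0.515 × 0.30) = −2.96.
- Drop-out of 25/25/27/33/40% from placebo to 160 mg (mean 30%), early leavers: 120 mg gives −13 × (1 − 0.515 × 0.33) = −10.79 and 160 mg gives −13.5 × (1 − 0.515 × 0.40) = −10.72, so the order reverses. With leavers spread evenly it just holds (−11.14 against −11.16).
- Chance that the truly best dose ranks first in the early-leaver version (4,000 runs, SD 7 at Week 6, drop-out unrelated to score within arm): 0.61 with complete data, 0.55 with observed cases, 0.35 with LOCF. With drop-out rising only from 28% to 34%, LOCF gives 0.47.

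**5. The planned observed-case analysis.** The drop-out rates of step 3, run 4,000 times on unadjusted change (intermediate SDs of 4.5/5.5/6.5 assumed), gave a difference of 0.89 with LOCF and −0.03 with observed cases (SD 1.60). Observed cases therefore also remove the artefact when drop-out is unrelated to score. Score-dependent drop-out was not simulated.

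**The case against.** Much of the case for the plan is sound.

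- **LOCF does not stand alone.** An observed-data FAS analysis is planned, and the PPS uses observed data. Under the score-independent drop-out simulated here, observed cases would expose the distortion, and an MMRM adds mainly precision. This stands. But the protocol does not rank the two FAS analyses, and a completers-only Week 6 comparison does not handle drop-out that depends on earlier scores.
- **The bias between doses is conditional.** A reader might infer that LOCF does confound tolerability with efficacy here. The documents do not support that: they give no drop-out by dose, and the unequal rates above are assumed.
- **The carried share may be below 30%.** That figure is the upper end of a planning range, and the FAS excludes subjects with no post-baseline score.
- **For a last-on-treatment endpoint, the final score is the outcome itself.** That would be a defence if the protocol held to it, but its ANCOVA compares doses at the end of Week 6.
- **The trial is exploratory, and the LOCF default can be overridden elsewhere.** The first softens concern about type I error, not about choosing a dose. The second leaves room for the SAP to act, but the protocol has still fixed the default.

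Two further criticisms are tempting. One is that the "repeated measure analysis of variance (time as intragroup factor, treatment group as intergroup factor") omits baseline and site; the other is that the flow-chart heading "Visit 6/ at termination" would pass early scores off as Week 6 values. The first text names only the factors of an exploratory analysis. The second is a schedule of assessments, not an analysis-visit rule. Covariates and visit mapping are properly SAP detail, so neither is an error here.

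**Conclusion.** The point holds as a conditional risk that is worth removing. LOCF is the stated default in the primary set, 20-30% drop-out is planned for, and dose choice is the primary objective. If drop-out differs by 10-12 percentage points between two equally effective doses, LOCF creates a difference of about 0.6-0.9 HAM-D17 points. Where a dose is truly better by 0.5 points, about 6.5-8 percentage points of excess drop-out over a comparator at 25% would reverse the order.

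These sizes rest on assumed trajectories and drop-out patterns, not on figures in the protocol. The artefact is also below one SD of the estimated difference (0.92 against 1.36), and even complete data ranked the best dose first only about 61% of the time. It does not follow that the dose ranking will be wrong, or that LOCF always favours one dose.

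**What to change.** Name as the primary analysis an MMRM on the observed HAM-D17 changes at Weeks 1, 2, 4 and 6. Include treatment, visit, treatment-by-visit, baseline HAM-D17, baseline-by-visit and site, use an unstructured covariance, and report Week 6 contrasts with placebo. Keep LOCF ANCOVA and the observed-case analysis, both labelled as sensitivity analyses, so that their rank is clear.

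Align the endpoint wording at the same time. The MMRM estimates the Week 6 outcome, not the last on-treatment score, so Analysis of Efficacy and the Statistical analyses row of the Abstract should state one time point.

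The cost is wording in the protocol and SAP; no new data are needed. The MMRM relies on missing at random, and in the step 3 simulation the SD of the estimated difference rose from 1.36 to 1.41, about 4% (1.41/1.36 = 1.04).
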